### Outcomes

#### Primary Outcome

Difference in systolic blood pressure between the intervention group and control group at 15, 30, 45, 60, 75, 90, 105, and 120 minutes after each of 3 Red Bull (intervention group) or water (control group) ingestions as measured by the ambulatory blood pressure monitoring device.

#### Secondary Outcomes

Difference in the following postoperative variables between participants with or without postoperative intake of Red Bull energy drink:

Diastolic and mean arterial blood pressure at 15, 30, 45, 60, 75, 90, 105, and 120 minutes after each of 3 Red Bull (intervention group) or water (control group) ingestions as measured by the ambulatory blood pressure monitoring device.Postoperative heart rate (1/min) at 15, 30, 45, 60, 75, 90, 105, and 120 minutes after each of 3 Red Bull (intervention group) or water (control group) applications.Postoperative urinary output (mL) during the first postoperative 24 hours.Intraoperative and postoperative fluid administration (mL) until 24 hours after surgery.Intraoperative and postoperative administration of vasoactive drugs (mL) until 24 hours after surgery.Postoperative pain (NRS) during the first postoperative 24 hours.Rate of operative reexplorations during the first hospitalization (%): flap complications (%) and flap loss (%); total duration of hospital stay (number of nights spent at hospital); wound healing 4 weeks after surgery (photo documentation).

#### Other Outcomes of Interest

Patient- and tumor-related data, such as age, BMI (size and weight), tobacco use; diabetes mellitus, indication for surgery (oncologic or prophylactic), neoadjuvant chemotherapy, previous irradiation, side and type of flap, flap weight, and ischemia time will be assessed perioperatively or collected from the medical history.

#### Harm Outcomes

Differences in the incidence of notable adverse events between both groups. Adverse events include nervousness, nausea, anxiety, tremor, insomnia, arrhythmia, need for revision surgery, and flap loss.

### Frequency and Duration of Follow-up

The schedule of trial enrolment, interventions, and assessments are presented in Table 1. Following surgery, the study intervention will take place in the recovery room and on the ward of the 2 study sites. The follow-up ends 4 weeks post operation in clinic.

**Table 1 table1:** Schedule of enrolment, interventions, and assessments for the Red Bull study.

	First clinic appointment with the reconstructive team (preoperative)	Preoperative appointment with an anesthesiologist (up to 4 weeks before surgery)	Perioperative (treatment) period				Follow-up (4 weeks post surgery)
			Day of surgery	POD1^a^	Discharge from hospital		
Visit	1 (start)	2	3	3	3		4 (end)
Patient information and signed informed consent^b^	✓						
Demographic data	✓						
Medical history and letter from GP^c^	✓	✓					
Inclusion and exclusion criteria	✓						
Physical examination	✓						
Vital signs		✓ (provided by GP)	✓	✓			
Laboratory tests		✓ (provided by GP)					
Surgery (unilateral microsurgical breast reconstruction)			✓				
Administer Red Bull (intervention) or still water (control)			✓	✓			
Record blood pressure and heart rate			✓	✓			
Record urinary output			✓	✓			
Record volume of intravenous fluid administered			✓	✓			
Record volume of vasoactive drugs administered			✓	✓			
Record volume of oral fluid administered			✓	✓			
Record flap complications			✓	✓	✓		
Record operative reexploration			✓	✓	✓		
Record pain levels (NRS^d^ 0-10)			✓	✓	✓		
Record duration of hospital stay					✓		
Record adverse events of Red Bull ingestion			✓	✓	✓		
Assess wound healing and document photographically						✓	

^a^POD1: postoperative day.

^b^Informed consent form to be signed within 30 days of planned surgical procedure.

^c^GP: general practitioner.

^d^NRS: numeric rating scale.

### Recruitment

Participants are recruited for the study in outpatient clinic. All patients undergoing elective microsurgical breast reconstruction will be screened. Patients who consent to participate in the study are randomized at the moment of surgery planning. No compensation or payment is given to the study participants.

### Sample Size

The following assumptions estimated from literature and clinical experience:

Mean systolic blood pressure (mm Hg): We assume the same SDs (ie, 15) for both groups and the correlation coefficient among repeated measures to be 0.7. If we assume no differences in time in the control group (mean 115 mm Hg) and assume the difference between the intervention group and the control group to be about 10 mm Hg, the required sample size would be 27 per group.Heart rate (1/min): We assume the same SDs (10) for both groups and the correlation among repeated measures to be 0.7. If we assume no differences in time in the control group (mean 80/min) and assume the difference between the intervention group and the control group to be 5/min, the required sample size would be 46 per group.Vasoactive drug Ephedrine (mg): We assume the mean drug dose in the control group to be 63 and the mean drug dose in the intervention group to be 48. Assuming equal SDs (ie, 25) we get 45 per group.

The predefined parameters include a significance level (α level) of .05 and power (1-β) of 0.8.

We calculated the patients needed to be included using the application STATA (version 15.1; StataCorp, 2017; Stata Statistical Software: Release 15) and G*Power (version 3.1.9.4—a program written by Franz Faul, Universität Kiel). Considering the different calculations and accounting for potential missing data or dropouts, 50 patients per group will be included, leading to a total of 100 patients.

### Statistical Methods

We are planning to measure mean systolic blood pressure at 8 time points. For this, the right statistical model is a mixed ANOVA where the group is an independent (unpaired) factor, and the time is a dependent (paired) factor. The comparison of drug intake between the Red Bull group and the control group will be performed by student *t* test for independent data (assuming data will follow a normal distribution). In case data will not follow a normal distribution, an alternative nonparametric test will be used (Mann-Whitney *U* test).

### Analysis of Harm Outcomes

The frequency of adverse events and the number of patients experiencing events will be tabulated by relation to the study intervention (ie, as adverse reaction, serious adverse event, or serious adverse reaction) and by study group. Nonserious adverse events unrelated to the intervention are recorded in the medical notes only.

### Handling of Missing Data and Dropouts

If vital data relevant for the calculation of the primary and secondary end point are missing (ie, blood pressure recordings) patients will be excluded from the participant list. Dropouts will be replaced by consecutive patients.

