### Inclusion and Exclusion Criteria

Textbox 1 shows the inclusion and exclusion criteria.

As a standard of care, all patients are asked to perform a check-up by their general practitioner (GP) within 2-4 weeks before the microsurgical procedure. Their GP fills in a standardized form provided by the Institute of Anesthesiology, from which all inclusion and exclusion criteria can be drawn. Additionally, the GP performs an electrocardiogram and a blood test (complete blood count, electrolytes, creatinine, and international normalized ratio or Quick) for the patient and sends the result to the institute of anesthesiology at the respective clinic.

Inclusion and exclusion criteria.

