### Randomization and Blinding

Randomization is undertaken with equal allocation to each study group (Red Bull:still water=1:1) using a computed code. Blinding or masking is not feasible.

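### Excluding randomised women whose blood pressure recordings are missing, and replacing dropouts, lets events after randomisation decide who is analysed in an open-label trial

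*Protocol article*

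**What the plan says.** The rule stands in the protocol article under Handling of Missing Data and Dropouts. Where data vital to the primary and secondary end points "are missing (ie, blood pressure recordings) patients will be excluded from the participant list. Dropouts will be replaced by consecutive patients".

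Other sections fix the setting:

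- **Timing (Recruitment).** "Patients who consent to participate in the study are randomized at the moment of surgery planning". Surgery, the drinks and every recording come later.
- **Allocation (Randomization and Blinding).** "Randomization is undertaken with equal allocation to each study group (Red Bull:still water=1:1) using a computed code", and "Blinding or masking is not feasible". Overview also calls the trial open-label.
- **Model (Statistical Methods).** For systolic pressure at 8 time points, "the right statistical model is a mixed ANOVA".
- **Number of readings (Primary Outcome).** Eight readings after each of three drinks.
- **Outcomes that need no blood pressure reading (Secondary Outcomes, Harm Outcomes).** These include re-exploration, flap loss, pain, hospital stay and adverse events.
- **Sample size.** The 50 per group already contains an allowance for missing data and dropouts.

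**The concern.** The rule removes a randomised woman from the list of participants, not only from the blood pressure model. The trigger is something that happens, or fails to happen, after allocation is known. Randomisation makes the two groups comparable as allocated; it does not make comparable the subsets that finish with usable recordings.

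Two things are at stake. First, the systolic difference is biased if the chance of losing recordings differs between arms and is related to a woman's pressure. Second, women may vanish from outcomes that could have been observed in them. Other Measures of Minimizing Bias foresees return to theatre for flap complications in the first 24 hours. A woman re-explored during a drink or reading window could lose readings, and under the rule as written her re-exploration would leave the data with her.

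This is a stated rule, not a detail left to an unseen analysis plan.

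**Working it through.** **1. The plan's own figures.** Inputs from Sample Size: SD 15, correlation 0.7 and difference 10 for systolic pressure; SD 10, correlation 0.7 and difference 5 for heart rate; 63 against 48 mg with SD 25 for ephedrine; α 0.05 (two-sided assumed); power 0.80. Eight readings are taken from Statistical Methods.

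- SD of a woman's mean over 8 readings = SD × √((1 + 7 × 0.7)/8) = SD × √0.7375. This is 12.88 mm Hg for systolic pressure and 8.59/min for heart rate.
- n per group = 2 × (1.96 + 0.842)² × SD²/difference².
- Systolic: 2 × 7.849 × 165.9/100 = 26.05, so 27 (stated 27).
- Heart rate: 2 × 7.849 × 73.75/25 = 46.3, so 47 (stated 46).
- Ephedrine: 2 × 7.849 × 625/225 = 43.6, so 44, or 45 by noncentral t (stated 45).

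The stated sizes reproduce within rounding. No figure is in dispute.

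**2. Is replacement needed?** Power by noncentral t:

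| Per group | Systolic | Heart rate | Ephedrine |
|---|---|---|---|
| 50 | 0.97 | 0.82 | 0.84 |
| 45 | 0.95 | 0.78 | 0.80 |
| 31 | 0.85 | 0.62 | 0.64 |
| 27 | 0.80 | 0.56 | 0.58 |

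The primary comparison can lose (50 - 27)/50 = 46% of each arm before power falls to the stated level. The two secondary outcomes have much less slack.

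**3. Bias from selective exclusion (all rates assumed).** Take no true difference. Let a fraction e of an arm be excluded on a latent risk that correlates -0.5 with the woman's mean pressure, and replace until 50 are retained. The retained mean rises by 0.5 × 12.88 × φ(c)/(1 - e), where c is the standard normal (1 - e) quantile. The ratio φ(c)/(1 - e) is 0.1086 at 5%, 0.2743 at 15% and 0.4237 at 25%.

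- 5% against 15%: 6.44 × (0.2743 - 0.1086) = 1.07 mm Hg.
- 5% against 25%: 6.44 × (0.4237 - 0.1086) = 2.03 mm Hg.
- 10% in both arms: 0.

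A simulation of 6,000 trials per scenario gave shifts of 1.04, 2.06 and about 0 mm Hg, and type I errors of 6.8%, 12.4% and 4.7%. The sign depends on which arm loses more women: heavier loss among controls hides a benefit of the drink, heavier loss in the Red Bull arm imitates one. Replacement was built into the simulation and did not remove the shift.

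**4. How many women could the rule reach?** The article does not say how much must be missing. If one missed reading is enough, and readings fail independently at rate p (both assumed), the complete fraction is (1 - p)^m:

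| p | m = 8 | m = 24 |
|---|---|---|
| 1% | 92% | 79% |
| 2% | 85% | 62% |
| 5% | 66% | 29% |

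If only the loss of a whole recording counts, far fewer women are affected. A mixed ANOVA in its classical form also drops incomplete records, so the model does not soften the rule.

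**The case against.** Several objections are fair.

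- **Return to theatre.** A reader might infer that the rule removes precisely the women who are re-explored, so that flap outcomes are emptied. The documents do not support that. Nothing says that such a woman loses her recordings or counts as a dropout. The monitor is worn for 24 hours, while re-exploration is counted over the whole first hospital stay. A woman re-explored later, or between drink windows, can have complete readings. What stands is that the rule may selectively remove some women re-explored during monitoring.
- **Harm tables.** Analysis of Harm Outcomes states no restriction to women with recordings. Their loss from these tables follows from removal from the participant list, and the article does not say it outright.
- **Strict trigger.** The text speaks of missing recordings, not of any single reading, and Statistical Methods names 8 time points, not 24. The 24-reading column above is therefore an extreme.
- **Ineligibility.** The GP form, "from which all inclusion and exclusion criteria can be drawn", is completed 2-4 weeks before surgery. A reader might infer that women found ineligible after randomisation feed the same rule. Table 1 places the eligibility check at Visit 1, ticks the GP letter at Visits 1 and 2, and has consent signed within 30 days of surgery. The order is not established, and nothing sends ineligible women through this rule. It forms no part of this point.
- **Power.** A loss of power might seem the main harm. For the primary outcome it is not: 31 per group still gives about 0.85.
- **Equal loss.** If exclusion is the same in both arms and equally related to pressure, the bias is about zero.

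None of this rescues the rule. It leaves the validity of the comparison to an assumption about missingness that an unblinded trial cannot take for granted.

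**Conclusion.** The point holds as a defect in a stated rule. Exclusion and replacement after randomisation, without blinding, mean that the analysed groups need not be the randomised groups. The rule also gives a route by which observed clinical and harm events could be discarded for want of a blood pressure reading.

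Its size in this trial is unknown, because the article gives neither a missingness rate nor a re-exploration rate. Under the assumed scenarios the false systolic difference runs from about 0 (equal loss) through about 1 mm Hg to about 2 mm Hg, against a planned effect of 10, with type I error from about 5% to about 12%. These figures rest on the assumed exclusion rates, the -0.5 correlation and the plan's own SD and correlation. The direction cannot be stated in advance. The issue is bias and lost events, not power for the primary outcome.

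**What to change.** Replace the rule under Handling of Missing Data and Dropouts:

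1. Analyse every randomised woman in her allocated arm, and do not replace randomised women.
2. Fit a likelihood-based linear mixed model to all available readings in place of the complete-record mixed ANOVA, so that a woman with some missing readings stays in. A woman with no reading adds nothing to this model and should be reported by arm.
3. Count re-exploration, flap loss, pain, hospital stay and adverse events in every randomised woman, whether or not blood pressure was recorded.
4. Keep the complete-recording analysis as a sensitivity analysis.
5. Recruitment is complete and the database was locked in February 2023. Restore any randomised women who were excluded, and report exclusions and replacements by arm with reasons.

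The cost is a change of wording, some work to recover data, and possibly slightly wider intervals. The 50 per group already allows for missing data, and no further recruitment is needed for the primary outcome.

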### Ethics Approval

Ethics approval was granted from the Cantonal Research Committee, Switzerland (KEK-ZH 2020-00493). Patients receive an information sheet and provide informed consent before screening to participate in study-specific procedures. The study will be carried out in accordance with the protocol and with principles enunciated in the current version of the Declaration of Helsinki, the guidelines of Good Clinical Practice issued by ICH, the Swiss Law and Swiss regulatory authority’s requirements.

### Compensation

Participants will not be compensated for their participation in this scientific research project.

### Publication and Dissemination Policy

After the statistical analysis of this trial, the principal investigator will make every endeavor to publish the data in a medical journal. Participants will be informed about the outcome of the study once the trial results have been published.

## Results

Recruitment of the study participants started in June 2020 and was completed in December 2022. As described previously, there is evidence that Red Bull energy drink increases blood pressure in healthy volunteers and athletes [1,2]. We hypothesize that systolic blood pressure will be higher after each drink ingestion in the intervention group receiving Red Bull compared with the control group receiving still water. Red Bull could hence be used as a nonpharmacological adjunct to vasopressors or volume administration after microsurgical breast reconstruction. It could be particularly useful in settings where the postoperative use of vasopressors is limited.

## Discussion

The Red Bull study is a multicenter randomized controlled trial that will explore the effect of Red Bull energy drink intake on perfusion-related variables and flap outcome after microsurgical breast reconstruction. This paper describes the study protocol and statistical analysis plan. The trial sponsor is Plastic Surgery Group. Recruitment started on June 1, 2020, and completed in December 2022. Database lock and data extraction for analysis were carried out in February 2023 when all randomized patients completed the surgical procedure and follow-up period.

There is evidence that the Red Bull energy drink increases blood pressure in healthy volunteers and athletes [1,2]. We hypothesize that Red Bull will increase systolic blood pressure in women after microsurgical breast reconstruction. Red Bull could hence be used as a nonpharmacological adjunct to vasopressors or volume administration in women with hypotension after microsurgical breast reconstruction.

### Strengths and Limitations

This trial has some strengths. This is the first trial assessing the influence of Red Bull on perfusion-related variables after surgery. To minimize adverse events and limit premature dropout from the study, participants with allergies or intolerance to any component of Red Bull will be excluded from the study. Also, diabetes mellitus is considered an exclusion criterion. Red Bull contains 27.5 g of sugar per 250 mL. Patients with diabetes mellitus might require the intake of sugar-free Red Bull, which could, however, be associated with a different hemodynamic pathway [16]. Furthermore, patients with thyroid disease or patients requiring the intake of thyroid hormones will be excluded from this study as the intake of Red Bull was associated with an increased heart rate in a previous study [2]. This trial also has some limitations. Blood pressure is measured noninvasively, which might not be as precise as arterial blood pressure monitoring.

After the statistical analysis of this trial, the principal investigator will make every endeavor to publish the data in a medical journal. Participants will be informed about the outcome of the study once the trial results have been published. The reporting of results from the outlined statistical analysis will comply with the consolidated standards of reporting trials protocol.

## Appendix

Multimedia Appendix 1 Data Collection Form.

## Abbreviations

GP: general practitioner
NRS: numeric rating scale
